### **Participant randomization and recruitment**

Women will be selected randomly from the two sub-districts using the SEACO database as the sampling frame and then randomized to the intervention group (IG) or comparator group (CG) with a 1:1 allocation prior to being contacted. Randomisation will be conducted by a SEACO statistician ([name]) using Stata module RANDOMIZE without blocks [34]. Participant enrolment will be conducted by trained SEACO data collectors. All randomly sampled women who were then randomized to the IG or CG will be invited to participate by trained data collectors over the phone. The resources for this study do not permit separation of enrollment and data collection procedures and, so, DCs will be aware which group the women are assigned to and this aspect may increase the risk of bias. Participants and intervention providers will not be blinded during the enrollment and surveys. CHWs will not collect outcome measures. Women who agree to participate will receive an explanatory statement about the study and a token of appreciation for their participation.

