### *Intervention Group*

**Figure 1** demonstrates the intervention flow. Trained data collectors from SEACO will recruit women assigned to the IG via phone call and conduct a baseline survey with women who provide verbal consent to participate in the study. Data collectors will then send women from the IG group a text message that contains the link to the BCAC materials [36]. One CHW will be assigned to support between 50-60 women who agreed to participate. CHWs will call the women they have been assigned to in the same week to discuss BC symptoms and BSE, address any barriers to screening, and ask them whether they are interested in attending a CBE at the LPPKN clinic. If the participants are interested, CBE appointments will be offered to take place the following week at a time that suits the participant. CHW will address concerns of participants who are not interested in screening, but no further action will be taken by the CHW if participants refuse to attend the CBE. Nurses will ask women with normal CBE results to attend screening biannually as recommended in the clinical practice guidelines [37]. Women with abnormal findings during the CBE will see a doctor at the LPPKN clinic who will refer them to a hospital for a mammogram as soon as possible after their CBE, free of charge. Participants will be informed in private about their mammogram results by the LPPKN nurses and CHWs will not be informed of the result. CHWs will call women who do not attend the CBE to identify the reason for non-participation, address further barriers and reschedule the appointment if agreed with the participant. CBE positive women who miss their mammogram appointment will be called by the LPPKN nurses.

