### *Recruitment and training of CHW*

We aim to recruit 15-20 CHWs from the two study sub-districts. We will approach women aged 40-74 years from the SEACO community engagement committee (CEC) and ask them to participate as well as to identify other women who might be willing to be trained as a CHW for this study. CHWs will be recruited from different ethnic backgrounds to be matched with up to 60 female participants with the

same ethnic background and mother tongue (Malay, Cantonese, Hokkien, Tamil and English), which has been demonstrated to be more effective in increasing mammography screening uptake [38]. A recent review of CHWs reported that CHW-led interventions were associated with an increase in CBE and mammogram screening rates in 70% of the included research papers [14]. The CHW will be asked to confirm, prior to contacting the matched participants, that they have no pre-existing formal relationship with the participants (e.g. family relationship, teacher-student relationship, etc.), however, the CHW may be friendly with participants who live in the same neighborhood. CHWs will need to be literate, have access to a mobile phone and are able to attend all training sessions. CHWs will be asked to attend five hours of virtual training delivered over five consecutive weeks. A breast cancer surgeon, a public health physician, a staff nurse trained in health communication, a LPPKN nurse and a public health academic will train the CHWs on the basics of BC, CBE and mammogram screening, BSE, communication skills, how to address potential barriers and the importance of confidentiality. CHWs will practice their skills during role play using a prepared calling script to guide the phone conversation with participants. Two male volunteers will also participate in the CHW training and learn to speak to the participant's husbands or male relatives about participating in the study, if requested. Telephone conversations between the CHWs and participants will be recorded as per protocol. CHWs will receive a monthly phone credit and a one-off cash allowance for their time.

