### *Statistical analysis*

Quantitative data will be analysed with SPSS vs 24. Descriptive statistics at baseline will be reported as mean (SD) for continuous data and frequencies (percentages) for categorical data. The change in screening uptake and other outcomes will be compared between the IG and CG using student independent samples t-test and Chi-square tests. A Chi-square test will compare the proportion of IG and CG participants who attended CBE after completion of intervention delivery, approximately 4-6 weeks after completing the survey. The difference in proportion or odds ratio or relative risk (and 95% CI) will be used as an initial indicator of effect size and we will aim to estimate the 'number needed to treat' in terms of the number of patients that would need to be given the intervention for one extra to be screened (via CBE). Change within groups will be analysed using paired samples t-test for continuous variables and Chi-square test for categorical variables. Multivariate regression models will be used to investigate factors (e.g. ethnicity, age, income, marital status, education, BC history and BC screening history) affecting screening participation.

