### *Sampling size and procedure*

Women from Sungai Segamat and Jabi will be randomized to either IG (n=466) or CG (n=466) prior to recruitment. A sample of 1600 women (n=800 for the IG and CG) will be drawn from the SEACO database to account for participants who are not interested in participating. A sample size of 932 will allow 80% power to detect, as statistically significant at the 5% level, an increase of 9% or more in the proportion aware of a BC symptom in the IG compared to the CG after the intervention (based upon baseline awareness of a breast lump as a cancer symptom of 65% from our previous Newton-Ungku-Omar funded study). The sample size of 932 will also allow 80% power to detect an absolute increase in the proportion of women who avail of a CBE following receipt of the intervention of the intervention of 9% compared with the comparator group. The pilot will be tested with 40-50 participants.

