| CENP Intervention
Opportunities mapped onto the subcomponents of the COM-B model | LPPKN clinic has experienced nurses trained in CBE.

Participants will be referred to the BCAC website for information on BSE by the CHWs. | LPPKN clinic has experienced nurses trained in CBE.

Participants will be referred to the BCAC information website and will receive information from the CHWs. | CBE, mammogram and transport costs will be covered for participants.

Appointment scheduling to reduce waiting times and ensure staff availability | Trained CHWs will be matched with participants based on ethnic and language background.

Male CHWs will be trained to support husbands.

LPPKN nurses are all females. | Participants will be educated on BC risk and susceptibility by the CHWs.  | Barriers such as embarrassment and fear will be addressed by the CHWs prior to screening. |

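### Intervention women share community health workers, but the primary chi-square test and the sample of 932 treat all women as independent; if the workers differ in effectiveness, the interval is too narrow

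*Protocol*

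**What the plan says.** - **Allocation.** Women are individually "randomized to the intervention group (IG) or comparator group (CG) with a 1:1 allocation prior to being contacted" (Protocol, Participant randomization and recruitment).
- **Delivery.** In the IG, "One CHW will be assigned to support between 50-60 women who agreed to participate" (Intervention Group). That CHW talks through symptoms and barriers, offers a CBE appointment, and calls women who do not attend. The Comparator Group section gives CG women no CHW, only usual opportunistic screening.
- **Number and matching of CHWs.** "We aim to recruit 15-20 CHWs from the two study sub-districts" (Recruitment and training of CHW). In Table 1, "Trained CHWs will be matched with participants based on ethnic and language background".
- **Primary analysis.** "A Chi-square test will compare the proportion of IG and CG participants who attended CBE" (Statistical analysis). An effect measure with a 95% CI and a number needed to treat (NNT) accompany the test. The example covariates for the regression models do not include the CHW.
- **Sample size.** Women "will be randomized to either IG (n=466) or CG (n=466) prior to recruitment", and "A sample size of 932 will allow 80% power to detect" the target difference (Sampling size and procedure). For CBE uptake this is an absolute increase of 9 percentage points. No ICC, design effect or cluster allowance is given, and no control CBE rate.

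**The concern.** This is a partially nested design: IG women fall into groups that share a CHW, while CG women stand alone. The CHW acts directly on the primary outcome by persuading, booking and rebooking. If some CHWs do this better than others, attendance is correlated among women who share one, and the IG proportion varies more than the binomial variance in a chi-square test allows.

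At stake are the width of the interval around the uptake difference and the NNT, the size of the test in some circumstances, and the stated power. The protocol also leaves the number of groups and their size unsettled, so a reader cannot tell how large the effect of clustering would be.

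**Working it through.** **Inputs.** From the protocol: 466 women per arm, a 9-point increase, 5% level (two-sided assumed), 15-20 CHWs, 50-60 women per CHW. The 36% comes from Quantitative research: the share of women in the 2017 survey who had ever received a CBE. The ICC is an assumption, 0.01 to 0.05; the documents give none.

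**1. Reproducing the plan's figure.** With independent women and pooled variance under the null,

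n = [1.96·√(2p̄(1−p̄)) + 0.8416·√(p₀(1−p₀) + p₁(1−p₁))]² / (p₁−p₀)².

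For p₀ = 0.36 and p₁ = 0.45, p̄ = 0.405: n = (1.3607 + 0.5818)² / 0.0081 = 465.8, so 466 per arm. This matches exactly and leaves no room for clustering. The awareness inputs (65% to 74%) need only 410 per arm, so they do not explain 466.

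**2. Number of CHWs against caseload.** 15×50 = 750 and 20×60 = 1,200 women, against 466 in the IG. With all 15-20 CHWs in use, 466/20 = 23 to 466/15 = 31 women each. With 50-60 women each, 466/60 = 7.8 to 466/50 = 9.3, so about 8-9 CHWs. The stated caseload would suit the whole trial (932/20 = 47 to 932/15 = 62), but only the IG has CHWs.

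**3. Design effect, IG only.** DE = 1 + (m−1)·ICC, with m women per CHW.

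- Standard error ratio with equal arm variances: √((1+DE)/2).
- Type I error of the naive test when CHWs differ around a zero mean effect: 2·[1 − Φ(1.96·√(2/(1+DE)))].
- Power: Φ(0.09/SE − 1.96), with SE = √[(p₀(1−p₀) + DE·p₁(1−p₁))/466].

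| m | ICC | DE | SE ratio | Type I error | Power, 36% vs 45% |
|---|---|---|---|---|---|
| 23 | 0.01 | 1.22 | 1.05 | 6.3% | 76% |
| 31 | 0.05 | 2.50 | 1.32 | 13.8% | 56% |
| 50 | 0.01 | 1.49 | 1.12 | 7.9% | 71% |
| 60 | 0.05 | 3.95 | 1.57 | 21.3% | 42% |

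Worked example, first row: SE = √[(0.2304 + 1.22×0.2475)/466] = 0.0338; 0.09/0.0338 − 1.96 = 0.70; power 76%. A middle case, m = 55 and ICC 0.02, has DE 2.08 and power about 61-62%.

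**4. If the control rate is not 36%.** Take an assumed 10% against 19%. Power with independent women is about 97.5%. At ICC 0.02 it is 94% (m = 23) down to 85% (m = 60), yet with these arm variances the true SE is still 1.13 to 1.32 times the naive one. At ICC 0.05 power is 86-81% for m = 23-31 and 69-64% for m = 50-60.

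**The case against.** Several objections stand and limit the claim.

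- **The ICC is assumed.** Shared training, a prepared calling script and feedback from recorded pilot calls should narrow differences between CHWs. The text message link, free CBE and transport reimbursement do not depend on the CHW. At 36% uptake, an ICC of 0.05 means a between-CHW standard deviation of √(0.05×0.36×0.64) = 11 points; 0.01 means 5 points. The extremes of 21% type I error and 42% power combine the highest ICC with the largest caseload.
- **A reader might infer that the test's type I error must exceed 5%.** It need not. If CHWs do not differ, the chi-square test is valid. The inflated figures require CHWs who differ while averaging to no effect, so that some lower uptake.
- **A reader might infer that ethnic matching itself breaks the test.** It does not. Randomisation is individual, so the ethnic mix is balanced in expectation, and sorting IG women by ethnicity afterwards adds no variance to the arm comparison. Only differences caused by the CHWs do.
- **A reader might infer that one or two outstanding CHWs could produce the result.** At 36% uptake, significance needs about 1.96·√(2×0.36×0.64/466)×466 = 29 extra attenders. With 23-31 women per CHW, one CHW cannot supply them, and two would need 98% to 82% attendance. It becomes feasible only at 50-60 women, where two CHWs would each need to add 29 to 24 points.
- **The 36% is inferred.** It is ever-receipt, not uptake over about 4-6 weeks in a pandemic, so the loss of power is conditional.

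The reply that this can wait for a statistical analysis plan does not stand: the protocol itself names the test and fixes the sample size.

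**Conclusion.** The omission is certain from the text: neither the primary test nor the sample size allows for women sharing a CHW. Its consequences depend on how much CHWs differ. If they differ at all in effectiveness, the interval for the uptake difference and NNT is too narrow, by a factor of about 1.05-1.32 or 1.12-1.57 according to caseload, over the assumed ICC range. This does not depend on 36% being the control rate.

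The loss of power does depend on it. Because 466 has no slack at 36% against 45%, any positive ICC takes power below 80% on that basis. It would be too strong to say that the trial's 80% power is definitely not delivered, since the protocol never states the CBE control rate and a low rate would leave room. The mismatch between CHW numbers, caseload and IG size is a contradiction whatever the ICC. It would be tempting to set the caseload at 23-31, but the documents do not say which figure governs. The point calls for a change to the analysis, not to the design.

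**What to change.** - Record CHW identity for every IG woman; it is known from assignment.
- Make the primary analysis a partially nested model: a random CHW effect in the IG only, CG women as singletons, and small-sample degrees of freedom, since there may be as few as 8-9 CHWs. Adjust for ethnicity, because CHWs are matched on it and ethnic differences in uptake would otherwise be counted as differences between CHWs.
- Report the risk difference and NNT with the interval from that model. Keep the chi-square test as descriptive.
- Reconcile the CHW number and caseload in Intervention Group, Recruitment and training of CHW, and Figure 1 with the IG of 466.
- Restate the power with a stated control CBE rate for the outcome window, a caseload and an ICC range.

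The cost is analysis wording, a somewhat wider interval and a less favourable stated power. Randomisation and data collection need not change beyond keeping the CHW identifier.

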### **Intervention**

The evidence synthesis presents a clear narrative with respect to the need to educate rural women about BC screening and the importance of early detection of cancer combined with community navigation to encourage women to attend BC screening. IG and CG participants will be interviewed as baseline and at follow-up four weeks after intervention delivery has been completed.

Women who will be randomized to the IG will receive an intervention consisting of mHealth education and community navigation. Our previous mass media campaign, the Be Cancer Alert Campaign (BCAC), improved BC symptom awareness in Malaysia [10] and the BCAC website, video and brochure will be used to educate women as part of this study. Women face numerous emotional, practical, socio-cultural and health-system related barriers, and most recently, concerns related to the COVID-19 pandemic. We will train local female community health workers (CHWs) who will offer women two-way communication to address their fears and help them navigate the breast health care

system [35]. Additionally, we will train 1-2 male CHWs to engage with a woman's husband or male relatives if a woman communicates to her female CHWs that she would benefit from such engagement. There are a number of health system-related barriers and we will use the family planning clinic ran by the Ministry of Women, Family and Community Development (LPPKN) in Segamat to refer women for free CBE screening. A one-off reimbursement for transportation fees to the clinic will be offered to participants. Due to the COVID-19 pandemic and the MCO in Malaysia, the uptake intervention will be delivered through mHealth. A multi-component mHealth intervention will be used to promote screening and will include a combination of telephone calls and text messages to communicate with, and navigate, participants.

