#### ***Surveys (baseline and follow-up)***

The baseline and follow-up surveys will be completed over the phone. Trained SEACO data collectors will conduct telephone surveys with participants from the IG and CG that will take approximately 15-20 minutes. The follow-up survey will take between 20-25 min for the IG and 15-20 min for the CG. The surveys comprise a number of previously adapted and validated questionnaires. In order to ascertain changes in BC symptom recognition, we will include the validated Breast Cancer Awareness Measure for Malaysia (B-CAM-M) [41] before-and-after the intervention implementation. CBE and mammogram screening intentions at baseline will be measured by asking participants to respond to the statement 'I intend to have a Clinical Breast Examination to check for breast cancer in the near future', using a 5-point Likert scale (strongly disagree – strongly agree), providing the option 'I have not yet

thought about this'. Unless participants choose the last option, participants will also be asked at what age they are thinking of getting the CBE [42]. The same questions will be asked about participant's intention to attend mammogram screening. The follow-up survey will also include specific questions to assess participant satisfaction with the screening [43,44] as well as the acceptability and appropriateness of the intervention based on an adapted version of the validated Acceptability E-scale [45] (IG only).

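### The chi-square test named for within-group change in categorical outcomes does not suit before-after answers from the same women

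*Protocol*

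**What the plan says.** The Statistical analysis section of the protocol gives one sentence to before-after change inside each arm: "Change within groups will be analysed using paired samples t-test for continuous variables and Chi-square test for categorical variables".

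The data are paired by design. The Intervention section says "IG and CG participants will be interviewed as baseline and at follow-up four weeks after intervention delivery has been completed". The section on the baseline and follow-up surveys adds, for symptom recognition, that "we will include the validated Breast Cancer Awareness Measure for Malaysia (B-CAM-M) [41] before-and-after the intervention implementation".

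The Statistical analysis section also uses the chi-square test between arms, including for the primary outcome: "A Chi-square test will compare the proportion of IG and CG participants who attended CBE after completion of intervention delivery". McNemar's test, a marginal homogeneity test or any other paired method for categorical data is named nowhere in the protocol.

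**The concern.** The sentence respects the pairing for continuous outcomes and drops it for categorical outcomes from the same women. A Pearson chi-square test can be run on such data in two ways, and neither tests change properly.

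- **Time points as two independent samples.** The test ignores the positive correlation between a woman's two answers. Its standard error is too large, so its p-values are too large and real changes are more easily missed.
- **Baseline answer cross-tabulated with follow-up answer.** The test asks whether the two answers are associated. They nearly always will be, so it tends to give a small p-value whether or not anything changed.

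The two faults run in opposite directions, and the protocol does not say which table is meant. A reader of the results could not tell which way a reported p-value errs. At stake are the within-group p-values for items analysed as categories, such as recognition of a breast lump as a symptom, which the protocol itself handles as a proportion in its sample size section.

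**Working it through.** The protocol states no figure for this analysis, so there is none to reproduce. The check is how the named test behaves on paired data.

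**Inputs from the protocol (Sampling size and procedure)**
- n = 466 per group: "randomized to either IG (n=466) or CG (n=466) prior to recruitment".
- Level 0.05: "as statistically significant at the 5% level". Two-sided is assumed, as sidedness is not stated.
- Baseline recognition of a breast lump: 65%.
- Change of 9 percentage points. The protocol states this as a between-group difference. It is borrowed here as the only effect size given.

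**Assumptions, not in the protocol**
- Within-woman correlation ρ between the two binary answers, shown over a range.
- All 466 women in a group complete both surveys, which is the planned maximum.

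**1. Type I error if the time points are treated as independent.** With no change, the true variance of the difference in proportions is 2p(1−p)(1−ρ)/n. The unpaired test uses 2p(1−p)/n. Its true size is therefore 2[1 − Φ(1.96/√(1−ρ))], whatever p is.

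| ρ | 1.96/√(1−ρ) | True size, unpaired chi-square |
|---|---|---|
| 0 | 1.96 | 5.0% |
| 0.1 | 2.07 | 3.9% |
| 0.3 | 2.34 | 1.9% |
| 0.5 | 2.77 | 0.6% |
| 0.7 | 3.58 | 0.03% |

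Simulation (40,000 replicates, base rates 65% and 36%) agrees closely. On the same data McNemar's test rejects 4.7% to 5.2% of the time for ρ from 0 to 0.7.

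**2. Power for a change from 65% to 74%.** The joint probability of yes at both times is p11 = p1·p2 + ρ√[p1(1−p1)p2(1−p2)]. The discordant cells are b = p1 − p11 and c = p2 − p11.
- ρ = 0.3: p11 = 0.481 + 0.063 = 0.544, b = 0.106, c = 0.196.
- ρ = 0.5: p11 = 0.481 + 0.105 = 0.586, b = 0.064, c = 0.154.
- True SE of the change, √{[b + c − (c − b)²]/n}: 0.0251 and 0.0213.
- Null SE used by McNemar, √[(b + c)/n]: 0.0255 and 0.0217.
- Null SE used by the unpaired test, √[2 × 0.695 × 0.305/466] = 0.0302 in both cases.

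Power is Φ[(0.09 − 1.96 × null SE)/true SE]. The table gives the simulated values. The formula gives the same to within 0.3 points.

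| Change from 65% | ρ | Unpaired chi-square | McNemar |
|---|---|---|---|
| 9 points | 0.3 | 89% | 95% |
| 9 points | 0.5 | 93% | 99% |
| 5 points (illustrative) | 0.3 | 34% | 49% |
| 5 points (illustrative) | 0.5 | 32% | 63% |

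**3. Baseline-by-follow-up cross-table, no change at all.** The association chi-square has a non-centrality of about nρ². At ρ = 0.1 this is 466 × 0.01 = 4.66, at 0.2 it is 18.64 and at 0.3 it is 41.94. Simulated rejection rates at 65% are 58%, 99% and 100%. The test detects that women answer consistently, not that they changed.

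**The case against.** The strongest reply is that McNemar's statistic is itself a chi-square, and that a sentence about change within groups which names a paired t-test shows that the authors knew the data were paired. The term may be loose naming, with the variant left to an analysis plan. That is possible, but the text gives it no support: the same section uses the same term for comparisons of independent arms. The protocol also does more than leave the test open. It names one.

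Four limits stand.

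- **False positives.** A reader might infer that the plan will declare unchanged items significant. That needs the cross-table reading, and nothing in the protocol points to it. If the time points are treated as independent samples, the error is conservative under positive correlation.
- **Size of the loss.** A reader might take a small assumed change and report a very large loss of power. The correlations and any change below 9 points are assumptions. At 9 points the loss is about 6 percentage points.
- **Reach.** A reader might infer that most secondary outcomes are affected. The protocol lists domains and does not fix how beliefs, barriers or breast self-examination are scored. Outcomes analysed as continuous scores get the paired t-test, and mammogram attendance is not a before-after measure.
- **Weight.** Within-arm tests do not estimate the randomised effect, so this is supporting analysis.

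**Conclusion.** The point holds as a wrong method named for one class of secondary analysis. With 466 complete pairs and an assumed correlation of 0.3 to 0.5, treating the time points as independent gives a true type I error of about 1.9% to 0.6%. Power for a 9-point change from 65% is 89% to 93% rather than 95% to 99%, and for a 5-point change 34% to 32% rather than 49% to 63%. If the cross-table is used, the p-value does not bear on change at all.

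It would be wrong to read this as a threat to the trial's main result. The primary CBE comparison and the other between-group tests involve independent arms, where chi-square is appropriate. The sample size statement, "A sample size of 932 will allow 80% power to detect", concerns differences between arms. The correlation is not in the protocol, and loss to follow-up would reduce the number of pairs. Both would alter the figures, but not the conclusion that paired categorical data need a paired test.

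**What to change.** In the sentence on within-group change, replace the chi-square test for categorical variables with:

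- **Binary items:** McNemar's test, with the paired difference in proportions and its 95% CI.
- **Items with more than two categories:** a marginal homogeneity (Stuart-Maxwell) test. This includes the screening intention items, because the surveys section adds to the five ordered responses an unranked option for women who have not yet considered the matter.
- **Wilcoxon signed-rank on intention:** only among women who give a ranked answer at both time points, and labelled as that subset.

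The between-group chi-square tests stay as they are. The cost is one sentence. These are standard procedures and need no extra data, participants or change to the sample size.
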